**Study Plan**

We propose a randomized study to evaluate changes in glucose, amino acid, and fatty acid metabolism at early and late stages after bariatric surgery. We will explore the mechanism(s) of changes in any of these substrates by examining alterations in the secretion and action of energy regulating peptides and of the inflammatory responses. Morbidly obese subjects will be divided into two groups with 150 participants in each arm; 75 Caucasian participants and 75 African American and Hispanics:

**Group I**: will undergo bariatric surgery (RYGB, VSG, AGB)

**Group II:** will undergo bariatric surgery (RYGB< VSG< AGB) combined with omentectomyThe study will include Caucasians, African Americans and Hispanics matched for BMI, gender and age. It will include short and long term aims with respect to the time after the surgical intervention in addition to the pre-operation basal period.

We will also obtain fat and muscle samples from normal weight individuals undergoing other abdominal surgery to serve as controls.

**Specific Aim 1: Determine the mechanism for the metabolic improvements after** bariatric surgery

Metabolic effects of the surgery will be examined at 4-weeks postoperatively, at a time when early improvements in insulin sensitivity are observed in the majority of Caucasian subjects and when changes in BMI or body composition are minimal. Subjects will also be studied at 6, 12 and 24 months when weight loss becomes significant. Subjects may also be asked to return at 3, 4, and 5 years post-operatively in order to continue to observe changes that occur in the long-term. We will evaluate which improvements following RYGB can be related to early alterations in specific energy-regulatory peptides and/or inflammatory factors and which simply follow the decrease in body weight.

**Specific Aim 2: Explore the mechanism for the blunted and delayed metabolic improvement after** bariatric surgery **in African Americans and Hispanics**

Comparison of the temporal changes in the metabolic profile will be made under matched experimental conditions for Caucasians, African Americans and Hispanics. Gene microarray analysis from two adipose tissue depots as well as skeletal muscle will be used to obtain an unbiased approach that will guide data interpretation.

**Specific Aim 3: Explore whether combining omentectomy with bariatric surgery helps accelerate and sustain post-surgical metabolic improvements especially in the more refractory African American and Hispanic populations**

Removal of the greater omentum will be combined with bariatric surgery randomly in a subgroup of subjects. We hypothesize that onset time and magnitude of the metabolic improvements (as in **Specific Aim 1**) in African Americans and Hispanics who undergo bariatric surgery combined with omentectomy will be comparable to Caucasians undergoing bariatric surgery alone (without omentectomy). As already indicated, the African American cohort of patients manifested significantly improved insulin sensitivity to glucose metabolism. We seek to test the mechanisms of improvement and to uphold the null hypothesis that the two said groups are comparable over time. In all three aims, the studies proposed include determination of the following parameters:

1. Regional fat stores and muscle distribution by body circumference measurements and DEXA scans
2. Adipocyte size, tissue macrophage content and macrophage gene expression
3. Diurnal and food-induced secretion of adipokines such as leptin, resistin and adiponectin
4. Diurnal and food-induced secretion of the energy regulating-peptides such as ghrelin and PYY
5. Kinetics of blood glucose, amino acids and fatty acids
6. Insulin responsiveness and secretion
7. Levels of inflammatory markers such as CRP, IL-6, TNF-α2R (measure of TNF-α in plasma)
8. **Animal Studies and Previous Human Studies**

**Describe the process and outcome of the animal and/or laboratory studies that have been done. Also, if any previous human studies have been done (e.g., Phase I, other phases maybe in a different population or for a different indication).**

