***Statistical Methods, Sample Size, and Power Estimates:*** We based sample size estimates on historical case volumes (>600 procedures per year), patient demographic distributions (70% Caucasian, 25% African American, 5% Hispanic, 80% female 20% male). Persons who consent to participate will be enrolled in both the short and long term phases of the study. We assumed attrition for the short-term phase, which entails data points through postoperative week four, to be negligible, and for the long-term study, which entails a two-year postoperative follow-up period, to be ~ 25% by postoperative month 24. We based this rate on reported attrition following bariatric surgery over a comparable time, and the rate is assumed to be comparable between experimental groups. Anticipated effect sizes were based on previous research or standard conventions for large, medium, and small effects *(Cohen 1988)*. Unless noted, power estimates were determined using standard methods and software (Power and Precision™ v. 2.0, nQuery Advisor™ v. 3.0) for non-directional tests at the 0.05 alpha level.

Demographic information such as age, race, and gender will be tabulated. Descriptive statistics, including means, standard deviations, and ranges for continuous measures, as well as percentages and frequencies for categorical measures will be presented. Statistical analyses will be performed using standard packages (SPSS or SAS).

**Specific Aim 1:** The short-term phase of the investigation will include a group of 66 Caucasians and group of 66 African Americans and Hispanics (each of the two groups randomized to 33 bariatric surgery and 33 bariatric surgery + omentectomy). The long-term phase of the investigation will include at least 100 patients (25 in each of the four racial and procedure groups).

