**Specific Aim 3:** Analyses addressing **Specific Aim 3** will be performed using the statistical methods described above for both the short and long term phases of the investigation (mixed-model repeated measures analysis of variance and mixed effects modeling). Two subject groups will be included in these analyses: (a) African American and Hispanic patients receiving bariatric surgery plus omentectomy, and (b) Caucasian patients receiving bariatric surgery without omentectomy. Our hypothesized mechanism for the effects of omentectomy and race implies that these two groups will experience comparable outcomes over time. Given our previous data, which demonstrated a large effect of race (d > 1.5) on weight reduction following bariatric surgery, and our hypothesis that omentectomy will blunt the disparity in African Americans and Hispanics, effect sizes were set at > 0.81. The power to detect an effect of group (d=0.81) on a within-subject contrast (change over time) in the short-term phase of the study (33 patients per group) is 90%. Power is 80% to detect a comparable effect (d=0.81) on any contrast in the long-term study (minimum group size = 25). In order to analyze the effect of omentectomy independent of race, a sample size of 11 participants per group would allow us to detect a 25% difference in insulin sensitivity between groups, with an *alpha* value of 0.05 and power of 80% (*beta* = 0.2). This is based on data on glucose kinetics obtained previously in obese participants (Klein 2004). A difference of this magnitude is clinically meaningful because it represents the lower end of the observed effect of current treatment strategies for insulin resistance, such as moderate weight loss (Kelley, 1993; Kirk 2009; Tiikkainen 2004; Ross 2000) and thiazolidinedione therapy (Schrauwen-Hinderling 2008; Li 2007; Coletta 2009) which increase hepatic and skeletal muscle insulin sensitivity by 25-50%.

1. **Privacy/Confidentiality Issues**

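### The Study Plan enrols 300 patients, but the power section rests on 132 enrolled and about 100 completers, and nothing reconciles the two

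*Protocol*

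**What the plan says.** Two parts of the protocol give an enrolment size.

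- **Rationale and Specific Aims, Study Plan:** "Morbidly obese subjects will be divided into two groups with 150 participants in each arm; 75 Caucasian participants and 75 African American and Hispanics". This gives 2 × 150 = 300 in total and 75 per race-by-procedure cell.
- **Statistical Considerations, Specific Aim 1:** "The short-term phase of the investigation will include a group of 66 Caucasians and group of 66 African Americans and Hispanics", with "each of the two groups randomized to 33 bariatric surgery and 33 bariatric surgery + omentectomy". This gives 66 + 66 = 132 in total, 66 per arm and 33 per cell. Then: "The long-term phase of the investigation will include at least 100 patients (25 in each of the four racial and procedure groups".

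The statistical section also states how the two phases relate: "Persons who consent to participate will be enrolled in both the short and long term phases of the study". It takes attrition to be negligible through week four and, for the two-year phase, "to be ~ 25% by postoperative month 24". Power is computed "for non-directional tests at the 0.05 alpha level" unless noted otherwise. Each race-by-procedure power is attached to a group size of 132, 66 or 33 (short term) or 100 or 25 (long term).

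The Specific Aim 3 paragraph adds a separate statement on the omentectomy effect irrespective of race: "a sample size of 11 participants per group would allow us to detect a 25% difference in insulin sensitivity between groups", at 80% power. It cites earlier glucose-kinetics data but gives no standard deviation.

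**The concern.** The two totals differ by a factor of more than two (300/132 = 2.27), and both are written as the size of the trial. A reader cannot tell from the protocol when enrolment is complete, or for which effect the trial is sized.

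The difference also has a cost in patients. Under 132, 66 people are allocated to omentectomy; under 300, 150 are, which is 84 more. The Risks section lists possible additional bleeding and longer anaesthesia for that procedure, and the protocol gives no sample-size reason for the additional 84.

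**Working it through.** **Step 1. Do the stated powers reproduce from their own group sizes?** All tests are two-sided at 0.05. Formulas:

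- Time effect: paired t-test, noncentrality = d × √n / √(2(1 − r)).
- Main and interaction effects: 1-df F test with four cells, λ = f² × N.
- Two-group effects: two-sample noncentral t, noncentrality = d × √(n/2), with n per group.

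| Statement | Inputs | Noncentrality | Stated | Recomputed |
|---|---|---|---|---|
| Short term, time | n = 132, d = 0.3, r = 0.35 | 3.02 | 85% | 85.1% |
| Short term, main and interaction | N = 132, f = 0.30 | λ = 11.88 | 92% | 92.8% |
| Short term, within race or procedure | 33 v 33, d = 0.70 | 2.84 | 80% | 80.0% |
| Long term, time | n = 100, d = 0.3, r = 0.45 | 2.86 | 83% | 80.9% (81.6% by normal approximation) |
| Long term, main and interaction | N = 100, f = 0.30 | λ = 9.0 | 84% | 84.4% |
| Long term, within race or procedure | 25 v 25, d = 0.81 | 2.86 | 80% | 80.1% |
| Aim 3, short term | 33 v 33, d = 0.81 | 3.29 | 90% | 90.0% |
| Aim 3, long term | 25 v 25, d = 0.81 | 2.86 | 80% | 80.1% |

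Seven of the eight reproduce. The long-term time effect is about two points high.

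**Step 2. Which total fits the plan's own attrition?**

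- From 132: 132 × 0.75 = 99, and 33 × 0.75 = 24.75. These match the 100 and the 25 per cell.
- From 300: 300 × 0.75 = 225, and 75 × 0.75 = 56.25, about 56 per cell. Going from 300 to 100 would need a loss of 1 − 100/300 = 67%.

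So 132 and 100 form one consistent set, and 300 stands outside it.

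**Step 3. What would 300 imply?** The same formulas with 75 per cell, and with 225 in total (56 per cell) at month 24, give:

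- Short term: 99.5% (time), 99.9% (f = 0.30), 98.9% (d = 0.70), and 99.9% for Aim 3 (d = 0.81).
- Long term: 99.0% (time), 99.4% (f = 0.30), 98.9% (d = 0.81).

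Effect detectable with 80% power, two-sample t:

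| Comparison | If 300 enrolled | If 132 enrolled |
|---|---|---|
| Procedure overall, short term | 0.32 (150 per arm) | 0.49 (66 per arm) |
| Within race, short term | 0.46 (75 per cell) | 0.70 (33 per cell) |
| Within race, month 24 | 0.53 (56 per cell) | 0.81 (25 per cell) |

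**Step 4. The 11 per group.** With n = 11 per group, 80% power needs d = 1.256. A 25% difference then implies an SD of 25/1.256 = 19.9% of the mean (20.9% by normal approximation). In reverse, SDs of 19%, 20% and 21% give 10, 11 and 12 per group. The protocol states no SD, so the figure can be neither confirmed nor refuted.

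**The case against.** The strongest defence is that little depends on the discrepancy. Each power carries its own group size and nearly all reproduce. If 132 is right they stand; if 300 is right every one rises. Neither total leaves the trial short of power for its stated effects. The long-term numbers are also partly worded as floors, which 225 completers would satisfy. All of this is correct, and it limits the point to a contradiction about enrolment. It does not remove it. The short-term 66 and 66 are not worded as a floor, and because everyone who consents enters both phases, 132 is not presented as a sub-study of 300.

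A reader might infer three stronger points, which the documents do not support:

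- **That every stated power is indeterminate.** It is not. The open question is which total, and so which set of powers, belongs to the trial as run.
- **That 11 per group is a third enrolment target, so that stopping at 22 could be justified.** The sentence says only that 11 per group would suffice for one separate question. Both 66 and 150 per arm exceed it, no text makes 22 an analysis point, and the Randomization paragraph rules out interim analyses. Nor does it clash with 25 per group for d = 0.81, since a smaller group detects only a larger effect.
- **That 11 per group is underpowered.** This needs an SD that the protocol does not give. The fasting glucose in Table 1 (161±50, a coefficient of variation of 50/161 = 31%) is a different variable, measured in patients who all had type 2 diabetes, and cannot stand in for insulin sensitivity.

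**Conclusion.** The contradiction is established. The Study Plan's 300 conflicts with the 132 enrolled and roughly 100 completers on which the race-by-procedure powers rest, and no calculation in the protocol supports 300. The enrolment size is a basic design figure and is wrong in one of the two places, so it needs correcting.

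The size of the point is the gap between two designs: 300 against 132 patients, and a detectable within-race effect of 0.46 against 0.70 SD short term and 0.53 against 0.81 SD at month 24. It is not a finding of low power. A secondary correction is the long-term time effect, which is about 81% rather than 83% on the stated inputs.

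These figures assume equal cell sizes, two-sided 0.05, and the plan's 25% loss spread evenly over the cells. Which total the sponsor intended cannot be settled from the protocol. The agreement between 132, 25% attrition and 100 shows only which number the power section was built on.

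**What to change.** State one enrolment number, in the same terms, in the Study Plan and in the Specific Aim 1 paragraph of Statistical Considerations.

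- **If it is 132:** change the Study Plan to 66 per arm (33 per cell). The powers stand, apart from changing the long-term time effect from 83% to about 81%.
- **If it is 300:** restate the power section for 75 per cell short term (d = 0.46 detectable within race at 80% power) and about 56 per cell at month 24 (d = 0.53), and give the reason for sizing the trial at 300.

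In the same amendment, add the SD behind the 11-per-group sentence so that it can be checked; it need not be removed.

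The cost is amendment wording and, if 300 is kept, a recomputed set of powers. Correcting the text to 132 requires no further patients or procedures.

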***Role of RYGB in reversing T2DM in morbidly obese subjects:***Work performed by [name] recently followed 50 patients with T2DM before and after laparoscopic gastric bypass surgery. The aim of our prospective study was to analyze the efficacy of the procedure in reversing T2DM over a 6-month period. Gastric bypass normalized HbA1C levels and resulted in decreased fasting plasma glucose (p<0.00, for both). Complete resolution of T2DM, defined by normal levels of fasting plasma glucose and HbA1C after discontinuing medical treatment, was achieved in 70% of patients with T2DM. The rest of the patients showed partial responses determined by significant decrements in daily medications.

Multivariate analysis was then used to identify preoperative variables unfavorable for complete resolution of T2DM. The predictive value of each variable in relation to response type (full or partial) was expressed in odds ratio (OR), p value and confidence interval (CI) of 95% of OR. Univariate analysis revealed that (a) treatment with insulin, (b) waist circumference > 50 inches, and (c) levels of HbA1C≥ 8.0% were all associated (p<0.01) with partial responses. To eliminate the effect of confounding factors, we performed a multivariate analysis of the selected variables. The logistic regression model showed that the use of insulin and waist circumference greater than 50 inches remained statistically significant allowing the elaboration of a regression model to predict a full or partial response.

The analysis showed that patients with significant central obesity (waist circumference > 50 inches) when given insulin treatment are less likely to exhibit complete resolution of T2DM after gastric bypass surgery.

| **TABLE 1** | | |
| --- | --- | --- |
| **Variables** | **Baseline** | **6 Months** |
| **Fasting Plasma Glucose *(mg/dL)*** | 161±50 | 108±33 |
| **HbA1C *(%)*** | 7.5 ± 1.6 | 6.2 ± 1.2 |

| **TABLE 2** | | | | |
| --- | --- | --- | --- | --- |
| **Variables** | **χ2** | **P value** | **OR** | **95% CI** |
| **Age** | 2.9 | 0.085 | 0.930 | 0.85-1.01 |
| **Gender** | 0.07 | 0.81 | 0.83 | 0.2-3.9 |
| **Preop Insulin** | 9.4 | 0.002 | 9 | 2.2-36.5 |
| **Waist > 50 inches** | 11.2 | 0.001 | 40.4 | 4.6-352 |
| **BMI** | 3.2 | 0.074 | 1.08 | 0.99-1.2 |
| **Preop oral hypoglycemics** | 2.9 | 0.084 | 1.98 | 0.91-4.3 |
| **HbA1c > 8.0%** | 5.9 | 0.01 | 5.1 | 1.4-18.5 |

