***Enrollment for morbidly obese patients*:**

- Patients approved for RYGB, VSG, or AGB are reported to study coordinator
- Coordinator or study nurse screen subjects via Star Panel to determine eligibility

Subjects determined to be good candidates for the study are contacted and the study is described to them. If they show interest, detailed information, including the consent form, is sent to them to read over. The coordinator follows up to respond to questions or concerns.

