**Day of Surgery:**

- Subject is met in pre-op area and told about study. Subject is asked if he/she would be willing to let surgeon take muscle and fat samples during the operation. If subject agrees, he/she is consented and surgeon is notified.

**Randomization:** The randomization schedule will be generated by statistical software. The randomization code will be generated using a permuted block size of four. No other restrictions will be used. As each subject is recruited, the randomization is assigned by the coordinator and the surgeon is notified. The PI, [name], will not be involved in the selection and allocation of patients. All recruited patients and researchers involved in the evaluation of the end-points will be blinded to the treatment assigned throughout the whole study period. No interim analyses will be carried out during the course of this study.

1. **Study Procedures**

**Provide a description of what the participants will experience. For example, a description of the instructions that will be given to the participants, activities in which they will engage, the length and timing of involvement, and the circumstances under which they will provide data (e.g., phone calls, spending time in an uncomfortable position, group assessments, one-on-one interview, videotaping, audiotaping, etc.)**

***Subjects who participate in metabolic chamber (the subjects will be assigned to the metabolic chamber in the preoperative period and will have chamber studies again at 6-, 12-, and 24-months post-operatively, as well as 3, 4, and/or 5 years post-operatively, unless otherwise noted):***

**Study Day 0:** Subject reports to the GCRC in the afternoon. The following are performed:

- Measurements of Height, Weight, and Body Circumferences.
- History and Physical Examination
- Performance of EKG (if over age 40)
- Performance of serum pregnancy test (if fertile female)
- Answer SF-36 Questionnaire
- Orders will be written for no food and caffeine after 20:00. They will be made completely NPO after 24:00

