Initial analyses will examine the short-term effects of race and surgical procedure (bariatric surgery + omentectomy), and the interaction effect of race by surgical procedure on change in measures of body composition, inflammatory factors, hormones, energy-related peptides, and health-related quality of life following bariatric surgery. The general case statistical method is mixed-model repeated measures analysis of variance with tests of: (a) the within-subjects effect of time; (b) the between-subjects main effects race and surgical procedure; and (c) race by procedure by time interaction effects. Simple contrasts will be used to test effects at postoperative week four in relation to preoperative measure. Statistical tests of main and interaction effects of race and omentectomy on any contrast are analogous to interaction of these effects with the within-subject change scores (simple contrasts). Assuming a within-subject correlation between longitudinal data points that is as low as 0.35 in the combined sample (n=132), power is adequate (85%) to detect a small effect (d=0.3) of time for any contrast. Power to detect, for any contrast, medium (f=0.30) overall main effects of race and omentectomy and the race by omentectomy interaction effect is 92%. This statistical design will also be applied within each racial group (n=66) to more explicitly examine the effect of omentectomy, and within each surgical group (n=66) to more explicitly examine the effect of race. For these analyses, the power to detect medium to large (d=0.70) effects for any contrast is 80%.

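### Race groups are described as matched on BMI, gender and age, but no matching step is given and the 4-week and 24-month completer models do not adjust for them, so these race contrasts are open to confounding.

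*Protocol*

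**What the plan says.** **Matching.** The Study Plan (protocol, Rationale and Specific Aims) says the Caucasian, African American and Hispanic participants will be "matched for BMI, gender and age". Specific Aim 2 adds: "Comparison of the temporal changes in the metabolic profile will be made under matched experimental conditions for Caucasians, African Americans and Hispanics".

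**Enrolment.** Patients approved for surgery are reported to the coordinator. Then: "Coordinator or study nurse screen subjects via Star Panel to determine eligibility". Those judged good candidates are contacted. No matching variable, ratio, tolerance or selection rule is given. The eligibility criteria set an age range of 18 to 65 and no limit on BMI or gender.

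**Short-term analysis.** Under Statistical Considerations, Specific Aim 1: "The general case statistical method is mixed-model repeated measures analysis of variance". Its terms are the within-subject effect of time, then "b) the between-subjects main effects race and surgical procedure; and (c) race by procedure by time interaction effects". No baseline covariate is listed.

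**Long-term analysis.** The mixed-effects model uses five time points, including one month, and allows unnamed clinical covariates. The follow-up analysis of patients with complete data to month 24 returns to the short-term methods.

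**Aim 3.** African American and Hispanic patients with omentectomy are compared with Caucasian patients without it, using both the repeated-measures ANOVA and the mixed-effects model.

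**The concern.** Race is the subject of Aim 2 and defines the two groups in Aim 3, but it cannot be assigned. Protection against case-mix differences must come either from how patients are chosen or from the model. The protocol claims the first without describing it and leaves out the second in two of its three stated analyses.

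The protocol itself treats these factors as important. Both of its preliminary race comparisons (Preliminary studies) were matched on gender and BMI, and it calls BMI a major determinant of isoprostane formation. Inflammatory factors are among the 4-week outcomes.

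If the groups differ in BMI, sex or age, and these relate to the change after surgery, part of an unadjusted race difference reflects case mix. A reader told that the groups were matched would attribute all of it to race. In Aim 3, where comparable outcomes are the hoped-for result, an imbalance could also hide a real difference.

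**Working it through.** **1. The plan's own figures reproduce.** For the short-term race main effect, the inputs from Statistical Considerations are N = 132 in four cells, f = 0.30 and two-sided alpha 0.05. The noncentrality is N × f² = 132 × 0.09 = 11.88 on 1 and 128 df, which gives power 92.8% (stated 92%). For N = 100 it is 9.00, which gives 84.4% (stated 84%). For d = 0.70 with 33 per group, a two-sample t test gives 80.0% (stated 80%). The power arithmetic is sound. It contains no covariate or matching term and so assumes that the race contrasts are unconfounded.

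**2. What the 4-week contrast removes.** Testing change from the pre-operative value removes fixed differences in level between race groups. It does not remove differences in response that depend on BMI, sex or age.

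**3. Size of possible confounding (illustration).** The documents give no baseline data by race and no correlation between a baseline factor and change. Both inputs below are assumptions.

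- D = imbalance in the factor between race groups, in SD: 0.3 to 0.5
- r = correlation of the factor with the change score: 0.3 to 0.5
- Spurious race effect = D × r: 0.3 × 0.3 = 0.09 SD, up to 0.5 × 0.5 = 0.25 SD

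With n per group and no true race effect, the test statistic shifts by s = D × r × √(n/2). The rejection probability is P(Z > 1.96 − s) + P(Z < −1.96 − s).

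| Contrast | n per group | s at 0.09 SD | Error rate | s at 0.25 SD | Error rate |
|---|---|---|---|---|---|
| 4-week, race overall | 66 | 0.517 | 8.1% | 1.436 | 30.1% |
| 24-month completers, race overall | 50 | 0.450 | 7.4% | 1.250 | 24.0% |
| Aim 3, 4-week | 33 | 0.366 | 6.5% | 1.016 | 17.4% |

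For scale, f = 0.30 with two equal groups is d = 2 × 0.30 = 0.60. The spurious effect would be 0.09/0.60 = 15% to 0.25/0.60 = 42% of the race effect the study is powered to detect. A smaller assumed imbalance gives less: D = 0.25 with r = 0.2 gives 0.05 SD and an error rate of 5.9% at 66 per group.

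**4. Cost of adjusting.** Three covariate terms reduce the error degrees of freedom from 128 to 125. If the covariates explained nothing, power at f = 0.30 would still be 92.8%. If their joint correlation with change is 0.2 to 0.5, f becomes 0.30/√(1 − r²), or 0.306 to 0.346, and power is 93.7% to 97.7%. This assumes race groups balanced on the covariates. Imbalance would lower it somewhat.

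**The case against.** **Some selection does take place.** Good candidates are chosen after screening, and equal race groups cannot arise by taking all comers from a source population that is 70% Caucasian, 25% African American and 5% Hispanic. The missing mechanics therefore do not prove that no matching will occur. This stands, but selecting by race is not matching on BMI, gender and age, and no rule says which Caucasian patients are taken.

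**The randomisation text is not a contradiction.** A reader might set "The randomization code will be generated using a permuted block size of four" and "No other restrictions will be used" against the matching claim. Those sentences govern the allocation of omentectomy. Race is not allocated, so they can neither create nor rule out matching by race.

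**Not every analysis is unadjusted.** The long-term mixed model includes the one-month point, admits clinical covariates and also serves Aim 3. This stands, and it confines the point to the repeated-measures ANOVA and the completer analysis. An SAP, not shown, could name the covariates of the mixed model. The ANOVA, however, is specified in the protocol itself without any.

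**The protocol's own predictors are tempting evidence.** "The logistic regression model showed that the use of insulin and waist circumference greater than 50 inches remained statistically significant", with tabulated odds ratios of 9 and 40.4. These come from 50 patients, all with type 2 diabetes, and concern full versus partial resolution over six months. The waist interval runs from 4.6 to 352. They do not show how strongly baseline factors predict 4-week change here. The protocol also links response to fat distribution, so waist may lie on the pathway that Aim 2 explores, and fixed adjustment could remove part of the effect under study.

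**The size is assumed.** This is correct. The calculation shows what moderate imbalance would do, not that imbalance exists.

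**Conclusion.** The point holds in a limited form. The protocol claims a match that its enrolment text does not deliver and that its 4-week and 24-month completer models do not replace by adjustment. The race contrasts from those analyses, and from the repeated-measures part of Aim 3, are open to confounding of unknown size and direction. The 8% to 30% error rate at 66 versus 66 depends wholly on the assumed imbalance and correlation.

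A reader might infer that the race contrasts are biased. The documents do not support this, because they give no baseline comparison by race. Nor is the randomised omentectomy contrast biased: omitting covariates costs it at most some precision.

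This is more than missing detail, because the covariate-free model is stated and a better one is available from baseline data already planned. The change should be made, though it does not put the trial's randomised comparison in doubt.

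**What to change.** 1. In the Study Plan and Specific Aim 2, delete the matching claim or state that it is met by adjustment in the analysis.
2. In the 4-week repeated-measures model, the 24-month completer analysis and the Aim 3 models, include baseline BMI, sex and age as fixed covariates. Include their interactions with time as well, because a covariate main effect alone does not act on the change contrasts.
3. Use waist circumference and pre-operative insulin use at most in a prespecified sensitivity analysis, because they may lie on the pathway that Aim 2 explores.
4. Describe the race contrasts as adjusted observational comparisons, since adjustment for three factors leaves other differences between the groups open.

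The cost is wording and about three degrees of freedom per contrast. Height and weight are measured at the pre-operative visit, and age and gender are already to be tabulated, so no new data are needed.
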